#### 2.12.2 fNIRS data analysis

Functional near-infrared spectroscopy data will be preprocessed and analyzed using the NIRS-SPM toolbox in MATLAB. Raw optical density signals will first undergo quality assessment to identify and remove channels with excessive noise or poor signal quality, followed by motion artifact detection and correction, detrending, and band-pass filtering (0.01–0.1 Hz) to suppress low-frequency baseline drifts and high-frequency physiological noise such as heart rate and respiration. The preprocessed signals will then be converted into changes in oxy-hemoglobin and deoxy-hemoglobin concentrations using the modified Beer–Lambert law (Obrig and Villringer, 2003).

For task-related analysis, triggers sent at the onset of the Go and Go/No-Go phases within each block will be used to define events and construct an event-related design matrix. This design matrix will be convolved with a canonical hemodynamic response function, and a general linear model will be applied to estimate the amplitude of task-evoked hemodynamic responses for each phase at the individual subject level. The resulting parameter estimates will then be used for within-subject comparisons between Go and Go/No-Go phases, and for group-level statistical analyses to identify cortical regions showing significant task-related activation, with appropriate correction for multiple comparisons where necessary.

#### 2.12.3 EEG data analysis

Electroencephalography data will be processed in MATLAB/EEGLAB. After channel-wise quality control, electrodes exhibiting excessive noise or unstable impedance will be excluded. Ocular and motion artifacts will be identified and removed using independent component analysis. The data will then zero-phase band-pass filtered (0.5–45 Hz) and notch-filtered at 50 Hz to suppress line noise, before segmentation into pre- and post-stimulation epochs of equal duration.

For spectral characterization, power spectral density will be estimated with Welch’s method (Welch, 1967), and relative band power will be derived for delta (1–4 Hz), theta (4–8 Hz), alpha (8–13 Hz), beta (13–30 Hz), and gamma (30–45 Hz) ranges. Functional coupling between electrodes overlying the DLPFC and distributed cortical sites will be quantified using coherence and phase-locking value metrics. Time–frequency dynamics and spatial synchrony will be further summarized using event-related spectral perturbation and global field power, respectively.

Within-subject pre- versus post-stimulation differences will be assessed with paired statistical tests (paired *t*-test or Wilcoxon signed-rank test depending on normality), with false discovery rate control applied for multiple comparisons.

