Electroencephalography will be used to monitor cortical activity during ultrasound neuromodulation of the DLPFC at baseline, 2 weeks, and 4 weeks (Schlögl et al., 2016). Resting-state signals will be recorded continuously for 5 min before stimulation (baseline) and for 5 min immediately after stimulation. A 64-channel cap configured according to the international 10–20 system will be used, sampled at 1,000 Hz with electrode impedances kept <5 kΩ.

fMRI Acquisition

Functional magnetic resonance imaging will be used to evaluate changes in brain structure and connectivity. Scans will be performed at baseline and 4 weeks (Schlögl et al., 2016). Scanning will be performed on a 3T scanner with a 32-channel receive head coil. Each participant will first undergo high-resolution structural imaging for anatomical reference and spatial normalization. A multi-echo T1-weighted MPRAGE volume will be acquired (0.8 mm isotropic; TR = 2,500 ms; TEs = 1.81/3.60/5.39/7.18 ms; TI = 1,000 ms; flip angle = 8°; FOV = 256 mm; in-plane acceleration = 2), followed by a T2-weighted scan matched in resolution (0.8 mm isotropic; TR = 3,200 ms; TE = 564 ms; FOV = 256 mm; acceleration = 2). Auto-alignment to the AC-PC plane and vendor-supplied B0 shimming will be used prior to acquisition.

Resting-state fMRI will be collected with a multi-echo, multi-band gradient-echo EPI sequence (2.5 mm isotropic; TR = 1,670 ms; TEs = 15.6/38.2/60.8/83.4 ms; multiband factor = 4; in-plane acceleration = 2; echo spacing = 0.50 ms). To enable susceptibility-distortion correction, two runs (∼9 min, ∼300 volumes each) will be acquired with reversed phase-encoding directions (A→P and P→A) while keeping all other parameters identical. Participants will be instructed to keep their eyes open, fixate a central cross on a black background, remain awake, and minimize overt cognitive strategies. Head motion will be reduced using foam padding and a forehead strap; MR-compatible headphones/earplugs will provide acoustic attenuation.

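### As ordered in section 2.12.3, ICA is fitted before slow electrode drift is filtered out, which can leave some blink signal in the frontal EEG measures (minor, secondary outcome only)

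*Protocol article*

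**What the plan says.** Section 2.12.3 sets out EEG preprocessing as a sequence.

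- First, bad channels are dropped: "After channel-wise quality control, electrodes exhibiting excessive noise or unstable impedance will be excluded".
- Second, artifacts are removed: "Ocular and motion artifacts will be identified and removed using independent component analysis".
- Third comes the filter: "The data will then zero-phase band-pass filtered (0.5–45 Hz) and notch-filtered at 50 Hz". Segmentation into the pre- and post-stimulation periods follows.

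The cleaned signal then feeds spectral measures ("relative band power will be derived for delta (1–4 Hz), theta (4–8 Hz), alpha (8–13 Hz), beta (13–30 Hz), and gamma (30–45 Hz) ranges") and connectivity measures ("Functional coupling between electrodes overlying the DLPFC and distributed cortical sites will be quantified using coherence and phase-locking value metrics"). Section 2.7 places the DLPFC targets at F3 and F4, which are frontal sites.

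On acquisition, section 2.9.2 specifies a 64-channel cap, "sampled at 1,000 Hz with electrode impedances kept <5 kΩ", and the recording length: "Resting-state signals will be recorded continuously for 5 min before stimulation (baseline) and for 5 min immediately after stimulation". It states no amplifier high-pass. Neither section mentions EEG detrending or fitting ICA on a separately filtered copy. Table 2 lists EEG as a secondary outcome.

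**The concern.** ICA assumes a stable mixture with no more sources than channels. Slow drift that is specific to each electrode breaks that assumption and can take up much of the variance, so components are spent on drift and ocular components separate less cleanly. Filtering afterwards removes the drift itself but not the ocular signal left behind, because blink energy lies largely in the delta and theta range that the filter keeps.

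Two kinds of EEG measure are exposed. Residual blink adds to frontal delta and theta power and, since power is expressed relative to the total, shifts the other bands as well. It also adds a shared signal to coherence and phase-locking from electrodes over the DLPFC. The EEG tests named in section 2.12.3 are within-subject comparisons before and after stimulation, so added ocular noise bears directly on them.

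**Working it through.** The plan states no figure on this point, so there is none to reproduce. The check has four steps.

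**1. The order.** The word that opens the filter step places it after ICA. The band-pass is the only EEG drift removal stated anywhere. By contrast, section 2.12.2 names detrending for fNIRS.

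**2. What the order can change.** Let X be the data (channels × time), P the matrix that removes the chosen components, and F the temporal filter. Then P(XF) = (PX)F. Once P is fixed, filtering before or after component removal gives the same result. What matters is the data from which P is estimated. Read literally, that is X with its drift.

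**3. Source count.** If each of 64 channels has its own drift, there are 64 drift sources. One blink source makes 65, already more than 64 channels before any cortical source is counted.

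**4. Size.** The documents give no drift size, so the drift SDs below are assumptions. All runs used simulated EEG with channel-specific random-walk drift and removed the best-matching component or components. Sets 1, 2 and 4 used symmetric FastICA with the tanh contrast. Sets 1 and 2 had 100 µV blinks and drift below 0.3 Hz. Sets 1 to 3 report residual blink as a percentage of its original amplitude.

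| Set | Montage | Drift SD (µV) | ICA before filter | ICA fitted to high-passed data |
|---|---|---|---|---|
| 1 | 20 channels | 0 | 0.2% | 0.6% |
| 1 | 20 channels, all drifting | 20 / 50 / 100 | 2.5% / 8% / 43% | 0.6% throughout |
| 2 | 20 channels, all drifting | 20 / 50 / 100 | 2.2% / 6.2% / 31.5% | – |
| 2 | 20 channels, one fifth drifting | 100 | 15% | – |
| 2 | 64 channels, all drifting | 20 / 50 / 100 | 0.9% / 2.7% / 6.2% | about 0.45% |
| 2 | 64 channels, one fifth drifting | 20 / 50 / 100 | 0.1% / 0.2% / 0.2% | about 0.3% |
| 3 | 20 channels, all drifting | 20 / 50 / 100 / 200 | 2.5% / 7% / 17% / 94% | about 0.7% |
| 3 | 64 channels, all drifting | 20 / 50 | 2% / 5% | about 0.3% |

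Set 4 (20 channels, 240 s, 2 runs) used a different measure: residual ocular variance, blinks plus saccades, at 1–4 Hz in frontal channels.

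| Drift SD (µV) | ICA before filter | 0.5–45 Hz filter first | 1 Hz high-pass first |
|---|---|---|---|
| 0 | 0.01% | 0.02% | 0.02% |
| 50 | 2.69% | 0.04% | 0.04% |
| 200 | 55.06% | 0.23% | 0.19% |
| 1000 | 126.52% | 12.76% | 10.6% |

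Amplitude is the square root of variance, so 2.69% of variance is √0.0269 ≈ 16% of amplitude. Conversely, 6.2% of blink amplitude is 0.062² ≈ 0.4% of variance. The two scales should not be mixed. Set 4 also includes saccades and did not confine the drift to below 0.3 Hz.

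With drift on every channel, fitting ICA to high-passed data was better in every comparison. With no drift, or with drift on one fifth of 64 channels, the orders were practically equivalent. The size varied widely: at 100 µV it ran from 0.2% (64 channels, one fifth drifting) to 43% (20 channels, all drifting). Replicates were few (4 in set 1, 2 in sets 2 and 4), so the runs support direction rather than exact size.

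**The case against.** The strongest reply has four parts.

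- **Drift may be small.** Noisy or unstable electrodes are excluded before ICA, and impedance is kept low. Both act on drift, and with little drift the order hardly matters. This stands, and it limits the size of the problem.
- **The sentence does not say what ICA is fitted to.** Fitting on a high-passed copy, removing components from the unfiltered data and then band-passing is compatible with the stated order and, by step 2 of the working, equals the remedy. Such detail could sit in the manual of operations announced in section 2.13. This stands in part. A reader who follows section 2.12.3 literally would still fit ICA on drifting data, because the section commits to a sequence and mentions no such copy.
- **The montage has 64 channels.** Set 2 gave a much smaller residual with 64 channels than with 20. This stands against quoting the 20-channel results as the trial's exposure, but not against the direction.
- **The comparisons offer some protection.** ICA precedes segmentation, so one decomposition shared by the pre and post recordings is the natural reading. The between-group analysis in section 2.12.1 would largely cancel artifact common to both arms. This mostly stands, although cancellation of bias does not remove the added noise.

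A reader might infer that ocular artifact necessarily stays in the frontal signal, that about 43% of it does, or that pre/post changes in blinking will pass as neural change. The documents support none of these. They give no drift size. The 43% comes from 20 channels that all drift at an assumed 100 µV. The last inference also needs both a material residual and a systematic shift between recordings, and neither is shown.

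**Conclusion.** The point holds in a conditional form. As written, section 2.12.3 fits ICA to data from which slow drift has not been removed. This can degrade ocular separation and leave some blink signal in frontal delta and theta power and in DLPFC coupling.

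The amount is unknown for this trial. It is negligible without drift. With drift on every channel, it is about 0.9% to 8% of blink amplitude at assumed drift SDs of 20 to 50 µV, and larger beyond that. Electrode exclusion, low impedance, or drift confined to a few channels reduces it. The conclusion assumes that no amplifier high-pass or filtered training copy is used, since neither is stated.

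Severity is minor. EEG is a secondary outcome, and the primary outcome, reaction time on the food Go/No-go task, is unaffected.

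**What to change.** In section 2.12.3, state that the 0.5–45 Hz band-pass, or at least its high-pass, is applied before ICA. Alternatively, state that ICA is fitted on a high-passed copy (for example at 1 Hz) and the resulting weights are applied to the 0.5–45 Hz data, from which the ocular and motion components are then removed. In set 4, moving the existing filter first gave nearly all the benefit: 0.04% and 0.23% at 50 and 200 µV, against 0.04% and 0.19% with a 1 Hz high-pass. If the team already works this way, only the description needs correcting.

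The cost is one sentence and negligible computing time, with no extra data.

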### 2.9 Outcome measures

An outline of the study outcome assessments and corresponding descriptions of their purposes is presented in Table 2.

**TABLE 2 T2:** Outcome assessments and their respective purposes.

Outcome measures	Assessment type	Purpose description
Food Go/No-go task	Primary outcome	To assess food-related inhibitory control
Body weight and BMI	Secondary outcome	To monitor physical changes related to the intervention
FCQ-T and FCQ-S	Secondary outcome	To evaluate long-term and situational food cravings, respectively
VAS	Secondary outcome	To measure appetite and hunger perceptions
DEBQ	Secondary outcome	To assess habitual patterns of emotional, external, and restrained eating
Stroop task	Secondary outcome	To measure cognitive flexibility and selective attention
fNIRS	Secondary outcome	To measure task-related hemodynamic responses in the cortical surface
EEG	Secondary outcome	To monitor cortical activity during ultrasound neuromodulation of the DLPFC
fMRI	Secondary outcome	To evaluate changes in brain structure and connectivity

LIPUS, low-intensity pulsed ultrasound; BMI, body mass index; FCQ-T, Food Cravings Questionnaire-Trait; FCQ-S, Food Cravings Questionnaire-State; VAS, visual analog scale; DEBQ, Dutch Eating Behavior Questionnaire; EEG, electroencephalography; fNIRS, functional near-infrared spectroscopy; fMRI, functional magnetic resonance imaging.

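### The EEG plan names global field power as its measure of spatial synchrony, but it measures field strength; electrode-level coherence and phase-locking can also shift with local power alone

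*Protocol article*

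**What the plan says.** EEG is a secondary outcome in Table 2 (section 2.9), with the purpose "To monitor cortical activity during ultrasound neuromodulation of the DLPFC". Section 2.9.2 describes a 64-channel recording: "Resting-state signals will be recorded continuously for 5 min before stimulation (baseline) and for 5 min immediately after stimulation".

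Section 2.12.3 derives three groups of measures from these recordings:

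- Power: "power spectral density will be estimated with Welch’s method (Welch, 1967), and relative band power will be derived" for five frequency bands.
- Coupling: "Functional coupling between electrodes overlying the DLPFC and distributed cortical sites will be quantified using coherence and phase-locking value metrics".
- Two further summaries: "Time–frequency dynamics and spatial synchrony will be further summarized using event-related spectral perturbation and global field power, respectively". The last word of that sentence ties global field power to spatial synchrony.

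The stated preprocessing is channel quality control, independent component analysis for ocular and motion artifacts, and band-pass filtering, with the data also "notch-filtered at 50 Hz to suppress line noise, before segmentation into pre- and post-stimulation epochs of equal duration". The stated test is: "Within-subject pre- versus post-stimulation differences will be assessed with paired statistical tests", with false discovery rate control.

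**The concern.** A measure of synchrony should respond to how signals at different sites relate in time, and should not respond merely because the signals become larger. Global field power fails that requirement by its definition. If stimulation, or any other difference between the two recordings, changes signal amplitude, the plan as written would report a change in spatial synchrony.

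The coupling measures raise a weaker version of the same issue. A single source seen by two scalp electrodes at zero lag contributes to both coherence and phase-locking value. If that source becomes stronger relative to everything else the electrodes pick up, both measures can rise although no two sources are coupled. This trial stimulates focally over the DLPFC and takes the electrodes above that site as seeds, so a local power change there is plausible.

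What is at stake is the label on a mechanistic result: a change in field strength or local power could be described as a change in synchrony or in network coupling.

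**Working it through.** The plan states no figure on this point, so there is none to reproduce. The check uses definitions first and then a simulation. The article does not define global field power; the standard definition is used.

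**1. Response to a uniform gain c**

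- Global field power at time t is √[(1/N) Σ (uᵢ(t) − ū(t))²]. Replacing every uᵢ by c·uᵢ multiplies it by c.
- Coherence is |Sxy|²/(Sxx·Syy). The gain multiplies numerator and denominator by c⁴, so coherence is unchanged.
- Phase-locking value is |mean of exp(i(φx − φy))|. Amplitude does not enter, so it is unchanged.
- Relative band power is a ratio of powers and is also unchanged.

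Numerically, over 64 average-referenced channels, global field power of 0.704 becomes 0.704 × 1.3 = 0.915. With a gain of 1.25 in the simulation of step 3, 1.206 becomes 1.508 (+25%), while phase-locking value (0.463) and coherence (0.326) do not move.

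**2. One shared source, no coupling**

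Let x = a·s + n₁ and y = b·s + n₂ with s, n₁ and n₂ independent, n₁ and n₂ of unit power, and s of power P. Then

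coherence = a²b²P² / [(a²P + 1)(b²P + 1)].

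With assumed weights a = 0.5 and b = 1.0:

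| P | Arithmetic | Coherence | Simulated coherence | Simulated phase-locking value |
|---|---|---|---|---|
| 1 | 0.25/(1.25 × 2) | 0.100 | 0.104 | 0.260 |
| 1.2 | 0.36/(1.3 × 2.2) | 0.126 | 0.130 | 0.285 |
| 1.5 | 0.5625/(1.375 × 2.5) | 0.164 | 0.163 | 0.322 |
| 2 | 1/(1.5 × 3) | 0.222 | 0.229 | 0.384 |

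The cross-spectrum a·b·P is real, so the imaginary part of coherency is zero in theory. Its simulated absolute value stayed at 0.027 to 0.033, which is estimation noise.

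**3. A 64-electrode layout**

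All of the following is assumed: electrodes on a ring, 12 mutually independent sources at 8–13 Hz, Gaussian field spread of 0.6 rad, sensor noise 0.5, average reference, 300 s, one realisation. The near pair is 6 electrodes apart and the far pair 16. Only amplitudes change; true coupling is zero throughout. GFP is global field power and PLV is phase-locking value.

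| Change | GFP | Near PLV / coherence | Far PLV / coherence |
|---|---|---|---|
| None | 1.206 | 0.463 / 0.326 | 0.149 / 0.041 |
| Whole signal ×1.25 | 1.508 | 0.463 / 0.326 | 0.149 / 0.041 |
| All sources ×1.25, noise fixed | 1.457 | 0.500 / 0.367 | 0.161 / 0.046 |
| Source between near pair ×2 | 1.318 | 0.610 / 0.510 | 0.147 / 0.038 |
| Source under seed ×1.25 | 1.228 | 0.489 / 0.355 | 0.173 / 0.054 |
| Source under seed ×1.5 | 1.254 | 0.517 / 0.388 | 0.200 / 0.070 |
| Source under seed ×2 | 1.317 | 0.573 / 0.460 | 0.256 / 0.109 |

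These factors are amplitudes: ×1.25, ×1.5 and ×2 are power factors of 1.56, 2.25 and 4. In these runs the absolute imaginary part of coherency stayed between 0.018 and 0.029 for the near pair and between 0.025 and 0.040 for the far pair.

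**The case against.** On global field power, the best defence is that stronger alignment of sources can enlarge the scalp field, so a rise is compatible with greater synchrony. That is true, but the measure cannot separate alignment from amplitude, and no detail in an unseen analysis plan would make the raw quantity do so.

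On coupling, the objections carry more weight, and most of them stand:

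- A reader might infer that any power change must reappear as a coupling change, so that one effect is counted as power, coupling and synchrony together. The definitions do not support this. Under a uniform gain, relative band power, coherence and phase-locking value all stay put and only global field power moves. Even doubling a source between the near pair left the far pair essentially unchanged.
- Field spread is set by anatomy and partly cancels in a within-subject comparison, unless source strengths or signal-to-noise ratio change.
- Coherence and phase-locking value are common electrode-level choices. Their weakness is a trade-off, not an error, and does not justify demoting them.
- Re-referencing, a Laplacian or source reconstruction may be specified in the full protocol or analysis plan. Their absence from a journal article is not a finding.
- Drowsiness between recordings should affect both randomised, blinded arms, and section 2.12.1 plans a between-group analysis. That protects a between-arm contrast from shared drift. It does not protect the paired test named in section 2.12.3, nor the interpretation of a real effect on local power.
- The article commits to explicit network hypotheses for fMRI (section 2.12.4) and not for EEG, so a mistaken EEG network claim is possible but not announced.

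**Conclusion.** The main point holds in full: section 2.12.3 assigns a field-strength measure to spatial synchrony. The measure rises in exact proportion to overall amplitude, so an amplitude change after stimulation would be reported as a synchrony change. This rests only on the standard definition of global field power.

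The coupling point holds conditionally. Coherence and phase-locking value can rise without true coupling when local source power or signal-to-noise ratio changes, mainly for nearby electrode pairs. The size depends on assumed source geometry. In the simulations, coherence moved from 0.10 to 0.13 for a 20% rise in shared-source power, and from 0.33 to 0.46 (near) and 0.04 to 0.11 (far) for a fourfold rise in power under the seed. These figures show direction and plausible scale; they do not predict this trial's data.

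The consequence is confined to how one secondary mechanistic outcome is interpreted. The primary outcome and the sample size are unaffected.

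**What to change.** In section 2.12.3:

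1. Report global field power as global field strength, and no longer as the summary of spatial synchrony.
2. Summarise spatial synchrony with an amplitude-independent measure from the same recordings, for example a zero-lag-insensitive index averaged over electrode pairs.
3. Keep coherence and phase-locking value for coupling. Add the imaginary part of coherency or the debiased weighted phase-lag index as a check.
4. Interpret a coupling change as a network effect only if it also appears in the added measure, and report it next to the power change in the same band.

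The cost is a change of wording and a little more analysis; no new recordings or visits are needed. The added measure misses genuine zero-lag coupling, so its failure to show a change does not prove that coupling is unchanged.

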Low-intensity pulsed ultrasound (LIPUS) is an emerging non-invasive therapeutic modality that applies ultrasound waves with low intensity and pulsed frequency to stimulate tissues at a cellular level. Traditionally used in musculoskeletal rehabilitation for its ability to promote tissue healing and reduce inflammation (Qin et al., 2023), LIPUS has recently attracted attention for its potential in modulating brain activity and improving cognitive function (Zeng et al., 2022). By fine-tuning parameters such as intensity, frequency, pulse width, and duration, LIPUS enables bidirectional modulation of targeted brain areas (Dallapiazza et al., 2018), including the DLPFC. Compared to traditional neuromodulation techniques, LIPUS offers deeper tissue penetration and localized stimulation without the need for invasive procedures (Tufail et al., 2011). Moreover, LIPUS operates intermittently, minimizing thermal effects and allowing precise stimulation without damaging surrounding healthy tissue (Fomenko et al., 2018). Research has demonstrated the potential of LIPUS to improve cognitive function in diverse groups, including individuals with Alzheimer’s disease (Shimokawa et al., 2022), as well as those with traumatic brain injury (Wang W. et al., 2024; Su et al., 2017). However, no studies have yet investigated the application of transcranial ultrasound therapy for improving executive function in individuals with obesity.

Therefore, the purpose of this study is to explore the efficacy of LIPUS as a potential non-invasive intervention to improve executive function in obesity, utilizing a self-developed wearable LIPUS device specifically designed for this purpose. We hypothesize that 4 weeks of daily LIPUS stimulation targeting the DLPFC will enhance executive function, as reflected by shorter reaction time in the Food Go/No-go task in the LIPUS group, whereas no significant changes are expected in the sham group. Furthermore, these improvements in executive function are expected to facilitate reductions in body weight and BMI.

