### 2.7 Intervention

Participants will perform LIPUS therapy independently at home over a 4-week period, utilizing a self-developed wearable device (Figure 2). The LIPUS group will receive pulsed therapeutic ultrasound, targeting the bilateral DLPFC projections on the scalp. The LIPUS device operates at a frequency of 600 kHz with an effective intensity of 1.0 W/cm^2^ and a 50% duty cycle (10 ms on, 10 ms off). Two transducers work alternately (each active for 1 s) during a 20-min treatment session, maintaining the treatment-site temperature below 41 °C to ensure safe and stable acoustic stimulation (Hayner and Hynynen, 2001; Zhang et al., 2021; U.S. Food and Drug Administration, 2019; Fomenko et al., 2020; Legon et al., 2020; Pellow et al., 2024). Each session will last 20 min, performed daily over 4 weeks. Treatment settings will remain unchanged throughout the trial unless the participant’s condition worsens or adverse effects are observed. The sham group will use a device identical in appearance and operation to the LIPUS group’s device but delivering no therapeutic ultrasound. All participants, regardless of group allocation, will receive standardized guidance on a low-calorie diet and maintenance of their habitual physical activity. This guidance is consistent with participants’ usual routines, and no additional dietary or exercise interventions will be applied. Participants will remain at home throughout the study, and will be asked to maintain daily logs of food intake and physical activity, which will be collected and reviewed regularly by the study team throughout the study period, ensuring that any observed differences in outcomes can be attributed to LIPUS stimulation.

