Primary within-subject contrasts will evaluate pre- vs. post-stimulation changes in (i) DLPFC-sgACC coupling (*a priori* expectation: stronger anticorrelation post-stimulation), (ii) DLPFC interactions with executive and default-mode networks (hypothesized ECN-DMN rebalancing), and (iii) whole-brain seed-to-voxel effects from the stimulated DLPFC. Group inference will use mixed-effects GLMs; voxelwise maps will be thresholded with permutation testing (≥5,000 permutations, TFCE), and ROI-level tests will controll FDR *q* < 0.05. We will report effect sizes for paired contrasts (Cohen’s dz) and 95% CIs. Robustness will be assessed by repeating models with/without GSR and by varying DLPFC seed radius (4 - 8 mm).

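### For EEG and fMRI, both secondary outcomes, the modality-specific analyses test change within subjects and name no LIPUS-versus-sham contrast, so changes shared by both arms could be credited to ultrasound

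*Protocol article*

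**What the plan says.** **EEG.** Section 2.9.2 sets the recording scheme at baseline, 2 weeks and 4 weeks: "Resting-state signals will be recorded continuously for 5 min before stimulation (baseline) and for 5 min immediately after stimulation". Section 2.12.3 then gives the inference: "Within-subject pre- versus post-stimulation differences will be assessed with paired statistical tests". The test is a paired t or Wilcoxon signed-rank test, depending on normality, "with false discovery rate control applied for multiple comparisons". Arm is not mentioned.

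**fMRI.** Scans are taken at baseline and 4 weeks only (Table 1 and section 2.9.2). Section 2.12.4 states: "Primary within-subject contrasts will evaluate pre- vs. post-stimulation changes in (i) DLPFC-sgACC coupling". It extends the same pre/post contrasts to executive and default-mode network interactions and to whole-brain seed effects, and reports Cohen's dz for paired contrasts. It adds "Group inference will use mixed-effects GLMs", without naming an arm or arm-by-time term.

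**General rule.** Section 2.12.1 provides between-group t-tests or non-parametric tests for continuous data, and a repeated-measures ANOVA comparing the two groups over three assessment times. It names neither EEG nor fMRI. Table 2 lists both as secondary outcomes.

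**Conditions common to both arms.** Both arms use devices that look and operate alike. Section 2.7 also says: "All participants, regardless of group allocation, will receive standardized guidance on a low-calorie diet".

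**The concern.** The sham arm shows what happens to these measures over the same interval without therapeutic ultrasound. A paired pre/post test asks only whether the measure moved. It gives the same answer whether the movement came from ultrasound, the passage of time, repeated sessions and recordings or, for the 4-week fMRI change, dietary guidance that both arms receive. FDR control and permutation thresholds limit false positives across many tests, but they do not remove a real change that both arms share.

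This matters because the abstract and the discussion present the neuroimaging as evidence of what ultrasound does to the brain. If sections 2.12.3 and 2.12.4 are followed as written, a significant paired result could be reported as such evidence although sham participants changed just as much.

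**Working it through.** **1. What the planned size was built on.** Section 2.11 gives f = 0.25, correlation 0.4, non-sphericity correction 1, 80% power, two-sided alpha 0.05 and 20 per group. For a within-between interaction with k = 2 arms, m measurements and N = 40:

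- Noncentrality: lambda = f² × N × m / (1 − rho); df = (k − 1)(m − 1) and (N − k)(m − 1).
- m = 2: lambda = 0.0625 × 40 × 2 / 0.6 = 8.33; df = 1 and 38; power 0.803. N = 40 is the smallest size reaching 80%.
- m = 3: lambda = 12.5; df = 2 and 76; power 0.884; N = 34 would suffice.
- A pure between-arm main effect would need N = 90 (m = 2) or 78 (m = 3).

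The stated 20 per group is therefore reproduced as a group-by-time interaction. That is the type of contrast missing from the EEG and fMRI sections. The sample size itself is not in dispute.

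**2. Does the general rule fill the gap?**

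| Measure | Timing | Test in its own section | Covered by the ANOVA in 2.12.1? |
|---|---|---|---|
| EEG, visit-level value | 3 visits | none separately stated | can be read so |
| EEG, change within a session | before/after, at each of 3 visits | paired test | not addressed |
| fMRI connectivity | 2 scans | within-subject pre/post, dz | not as worded (three times) |

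**3. Illustration of the consequence.** The documents give no expected change for EEG or fMRI, so the shift is an assumption. Inputs: no ultrasound effect; both arms shift by g = 0.3 or 0.5 SD; rho = 0.4, borrowed from the primary-outcome calculation; n = 20 per arm; one two-sided test at 0.05.

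- Standardised paired change: dz = g / √(2(1 − rho)) = g / √1.2.
- g = 0.3: dz = 0.274; noncentrality = 0.274 × √20 = 1.22; probability of significance in the LIPUS arm with 19 df = 0.214.
- g = 0.5: dz = 0.456; noncentrality = 2.04; probability = 0.491.
- Significant in LIPUS but not in sham, p(1 − p): 0.214 × 0.786 = 0.168; 0.491 × 0.509 = 0.250.
- The text does not say whether the arms are tested separately or pooled. Pooled (n = 40), the probabilities are 0.393 and 0.804.
- Between-arm t-test on change, simulated with 20 per arm, 40,000 runs and a shared dz of 0, 0.3, 0.5 or 0.8: rejection rate 0.049 to 0.051 throughout.

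**4. Price of the between-arm contrast.** Suppose the LIPUS arm truly changes by 0.5 SD of the change score and sham does not change. A paired test in 20 LIPUS participants has power 0.564; the between-arm test with 20 per arm has 0.338. At 0.8 SD the figures are 0.924 and 0.693.

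**The case against.** The strongest reply is that section 2.12.1 already promises two-group comparisons of outcome variables, that EEG and fMRI are listed outcomes, and that a condensed article may leave model terms to a fuller plan. Part of this stands. Visit-level EEG measures can be read as covered, and a mixed-effects GLM can carry an arm-by-time term; the text supports only that none is stated. But the article does fix the test for within-session EEG change and does label the primary fMRI contrasts. Both choices are within-subject, and the general rule fits neither.

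A reader might infer more than the documents support:

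- *That the sham control goes unused throughout.* It does not. Section 2.9.1 defines the primary outcome as LIPUS versus sham.
- *That fNIRS has the same fault.* Section 2.12.2 says: "The resulting parameter estimates will then be used for within-subject comparisons between Go and Go/No-Go phases". That contrasts task phases rather than times; group-level analyses are also planned, and fNIRS is measured at all three visits.
- *That the hypothesis shows the same fault in the imaging plan.* The words "whereas no significant changes are expected in the sham group" concern Go/No-go reaction time, for which the between-arm definition governs.
- *That diet explains EEG change.* The EEG pre/post change arises within one session, so diet guidance is not a plausible cause. It bears on the 4-week fMRI change, and even there section 2.7 describes the guidance as in line with usual routines.
- *That the percentages are error rates of the planned procedures.* They are for single tests, before FDR or permutation control.

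**Conclusion.** The concern holds for within-session EEG change and for fMRI. As written, their named inferences cannot distinguish an ultrasound effect from change common to both arms. Under the assumed shared shift of 0.3 to 0.5 SD, a single uncorrected paired test in the LIPUS arm would be significant about 21% to 49% of the time with no ultrasound effect, against about 5% for the between-arm test of change. These figures show direction and rough scale only: the shift is assumed, and the correlation comes from a different outcome. Severity is moderate, because only secondary outcomes are affected and both the primary outcome and the sample size are untouched.

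**What to change.** In sections 2.12.3 and 2.12.4, name the arm-by-time term as the inferential contrast: post minus pre in LIPUS, minus post minus pre in sham. For EEG, apply it to the within-session change. For fMRI, apply it to the change from baseline to 4 weeks, and state the arm term in the mixed-effects GLM. Attach the FDR and TFCE control already planned to this contrast, and report it with a 95% confidence interval. Keep the paired within-arm results and dz as description. The change should be made before unblinding.

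The cost is wording and contrast specification; both arms are already scheduled for these recordings, so no new data or participants are needed. The drawback is the lower sensitivity shown in step 4 of the working, which should be acknowledged when null imaging results are interpreted.
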